### Informed consent

Informed consent will primarily be received during a real-time telephone or video call using remote electronic consent (e-Consent) via DocuSign, although face-to-face and postal options may be used if requested. Consent for all participants under 16 years of age must be provided by a parent/legal guardian with confirmed parental responsibility. Current versions of the consent forms can be found in onlinesupplemental materials 1  2. Child participants will be invited to sign a paper assent form to affirm agreement if deemed developmentally appropriate. Ongoing eligibility and consent will be verbally re-confirmed at each study visit.

Copies of all completed consent and assent forms will be uploaded into the study database to enable remote central monitoring of the consent process. Enrolment of consenting participants in the study database will automatically generate a unique pseudonymised participant ID number.

### Randomisation

All enrolled participants will be randomised sequentially via the purpose-built secure web-based data capture system with integrated randomisation function held on REDCap Cloud (RCC; www.redcapcloud.com). This is a two-way crossover trial in which participants will be randomised to receive both the test and comparator study IMPs (Nasacthin and Synacthen), one per study visit, in a pre-determined, randomly allocated order. Full details of the randomisation schedule will be held in RCC and will not be routinely accessible to the study team.

### Trial investigational medicinal product (IMP)

The test IMP for the study is Nasacthin (Huddersfield Pharmacy Specials, Huddersfield, UK) and the comparator IMP is Synacthen (Atnahs Pharma UK, Basildon, UK). Details of administration are outlined in table 1. Nasacthin (500 µg tetracosactide+chitosan) will be administered via a primed intranasal Mucosal Atomisation Device (DART300, Pulmodyne, Indiana, USA) (0.1 mL to each nostril). Synacthen will be administered as a slow IV bolus via the indwelling cannula.

**Table 1 T1:** Trial investigational medicinal products

	Test IMP (Nasacthin)	Comparator IMP (Synacthen)
Constituents	500 µg tetracosactide + chitosan	250 µg tetracosactide
Administration route	Intranasal (via MAD)	Intravenous (via cannula)
Dose	0.2 mL (0.1 mL to each nostril)	250 µg (1 mL) for adults 145 µg/m^2^ for children

IMP, investigational medicinal product; MAD, Mucosal Atomisation Device.

The Nasacthin 500 µg dose is derived from previous pharmacodynamic work demonstrating a comparable plasma cortisol response to the SST at 60 min.^22^ Synacthen will be administered at the standard doses used for routine SST testing, that is, 250 µg (1 mL) in adult participants and 145 µg/m^2^ in children, as recommended in the British National Formulary for children (BNFc).^28^ The same doses have been adopted in the closely related STARLIT-2 study^26^ (which closed to recruitment in April 2025) to ensure directly comparable safety and efficacy data.

### Trial procedures

Trial participation is outlined in figure 1. Participants will attend two study visits with a minimum 3 day washout period between each visit to ensure elimination of any previous tetracosactide received and potential resultant effects on endogenous glucocorticoid levels. This was calculated based on the half-lives for both tetracosactide (34 min) and cortisol (120 min) from our previous studies^22^ and those reported in the literature.^29 30^ Five half-lives were taken as the period to minimal exposure/return to baseline (approximately ten hours), thus 3 days is thought to be a suitable washout period.

**Figure 1 F1:**
[figure not shown]
Flow diagram of participant trial procedures.

Due to potential interference with glucocorticoid measurement and in accordance with standard practice for an adrenal function test, participants will be asked to withhold their regular steroid medications taken for management of their AI prior to each visit (see table 2). This will be discussed with participants prior to consent and will be approved by their treating clinician prior to trial participation. Participants will bring their steroid medications to the study visit and take their next dose as soon as possible after collection of the final study samples.

**Table 2 T2:** Trial steroid medication omission guidance

Steroid type	Participant instruction
Oral Hydrocortisone	Omit the night/evening before and morning of each visit
Oral Prednisolone	Omit doses for 24 hours before visit
Oral Dexamethasone	Omit normal doses for 72 hours prior to each visit
Oral Fludrocortisone	Withhold administration the morning of the visit
Steroid creams, asthma inhalers, steroid nose sprays, steroid eye drops and all other non-oral steroids	Withhold administration the night before and morning of each visit
Parental steroids (except injectable hydrocortisone)	Can only participate 12 weeks after last injection

Participants will be contacted 1 week prior and 2 days prior to each visit to confirm attendance, provide important reminders regarding omission of steroid medications and check essential visit-specific exclusions. Any participants taking increased doses of steroids due to current or recent illness (‘stress dosing’) will be advised to reschedule the visit.

Participants will be asked to abstain from liquorice ingestion within the last week (preparations containing glycyrrhizic acid only due to its inhibitory effect on 11β-hydroxysteroid dehydrogenase type-2), and alcohol consumption and recreational drug use for 24 hours. Any Nasacthin visits will be rescheduled if a participant has experienced coryzal symptoms in the last week, a heavy nosebleed in the previous 48 hours, or has active allergic rhinitis (hay fever) symptoms requiring medication, due to their unconfirmed effects on nasal drug absorption.

Study visits will be scheduled to commence between 08:00 and 09:00 with the aim to collect baseline sample measurements while cortisol levels are close to their natural physiological peak to aid interpretation. A confirmed negative pregnancy test is required for all participants of childbearing potential before study activities can take place, due to the potential for altered cortisol levels and as per safety advice to avoid Synacthen administration in pregnancy where possible.

At the first study visit, basic demographic data, and height and weight measurements will be collected. The height and weight measurement will be repeated at subsequent visits for any child participants who have more than 3 months between visits.

At the start of each visit, a set of baseline clinical observations (temperature, pulse rate, blood pressure and respiratory rate) will be taken, and the date and time of last administration for all regular steroid medications will be checked and documented. The visit will be rescheduled if the participant is unwell or has not adhered to the steroid medication omission guidance.

Following IV cannulation, participants will rest supine for a minimum of 20 min. Ten minutes prior to commencing sample collection, participants will be asked to rinse their mouth thoroughly with water to minimise sample contamination. A pair of baseline blood and saliva samples will then be collected. Participants will be asked to refrain from eating or drinking within 30 min prior to baseline sample collection.

All whole blood samples will be collected from the indwelling cannula into serum separating tubes. Samples will be gently mixed and left to clot for 30–60 min at room temperature, before centrifuging at 1300 x*g* for 10 min. Resulting serum will be aliquoted into cryovials for storage. All saliva samples will be collected by passive drool into a Saliva Collection Aid (Salimetrics, Pennsylvania, USA) and may be centrifuged at 1000 rpm to reduce any bubbles if necessary. All samples will then be transferred to −80°C freezer storage prior to shipment to a central laboratory for analysis.

Study IMP will be administered immediately after baseline sample collection (as per table 1), in accordance with the allocated randomised sequence. Due to the effect of stress on cortisol levels, re-cannulation following cannula failure post-IMP administration is not permitted.

Further paired blood and saliva samples will then be taken at 30 min and 60 min post-IMP administration, with participants rinsing their mouth with water ten minutes prior to each saliva sample collection. Eating or drinking (except water) will not be permitted during the study sampling period. Participants will be advised to take their next doses of all regular steroid medications as soon as sample collection is completed.

All participants will receive a follow-up telephone call 24–48 hours (or next available working day) after each visit to check for the emergence of coryzal symptoms or any AEs.

In instances where individual study visits need to be repeated (eg, if requisite study samples cannot be collected), the same IMP will be administered at the repeated visit to maintain the allocated IMP sequence.

### Trial outcomes and assessments

Analysis of participant study samples for glucocorticoid levels will be performed at a central laboratory using liquid chromatography with tandem mass spectrometry (LC-MS/MS) assays to quantify the levels of serum cortisol, and salivary cortisol and cortisone. Optional consent for submission of any residual samples to a biorepository following completion of analysis will be obtained as part of the main consent process.

Cortisol levels at baseline and 30 min post-administration of Synacthen and Nasacthin will be used to determine the primary study endpoint, the PPA, which is defined as the proportion of participants known to have AI (as detected by the SST) correctly diagnosed by the Nasacthin test using the same threshold. This will also be measured as a secondary endpoint using the baseline and 60 min serum cortisol results as the current sampling timepoints for the SST. For the exploratory objective, serum cortisol, salivary cortisol and salivary cortisone levels at baseline and at 30 min and 60 min post-administration of Nasacthin and Synacthen will be used to produce summaries of the comparative responses.

Details of all harms or unintended effects occurring during trial participation will be collected and used to determine the frequency of AEs, SAEs and suspected unexpected serious adverse reactions (SUSARs) by treatment arm. Participants will be closely monitored for any AEs occurring following IMP administration, particularly in the first 30 min for any sign of hypersensitivity reaction. The follow-up telephone call will be used as a safety check for participants to report any AEs that may have occurred since the visit. Any harms or unintended effects that are considered serious will be logged electronically via the study database within 24 hours of first knowledge and reported as appropriate.

Participant evaluation of the acceptability and tolerability of Nasacthin administration will be sought using a short non-validated questionnaire to be completed at the end of each visit, and an additional questionnaire at the final study visit to compare the IV and nasal tests. Participants will also be invited to take part in a focus group for further exploration of these aspects.

At the completion of trial recruitment, healthcare professionals at participating sites will be asked to complete an anonymous online questionnaire on the comparative acceptability of administration of the two tests. To understand the utility and future barriers to adoption of the Nasacthin test, key stakeholders (eg, endocrinologists (paediatric and adult), nurses, clinicians from other heavy steroid-using specialties, pharmacists, biochemists, primary and community care providers, commissioners and service managers etc.) will be invited to attend focus groups to discuss the usability and practicalities of the different testing methods.

### Data collection and management

All information collected about participants during the trial will remain confidential and will be held in accordance with General Data Protection Regulation (GDPR) 2018. All study participants will be automatically assigned a unique identifying number at the point of enrolment onto the study database. All Hull Health Trials Unit (HHTU) data systems are within scope of the HHTU NHS Data Security and Protection Toolkit.

Study data will be collected and stored in a purpose-built, secure online electronic data capture system with integrated randomisation function and role-based user access held within the HHTU instance of RCC to enable central monitoring of trial recruitment and study visit completion. The database will be built and validated according to study-specific requirements outlined in a Data Management Plan agreed by the CI, Sponsor and HHTU. All activity within RCC is subject to a full user audit, with both automated and manual checks to monitor data quality and completeness according to a sponsor-approved monitoring plan.

Individual participant data will mostly be inputted directly into electronic case report forms held within the study database. Information on all AEs, SAEs and SUSARs occurring during the trial will be collected in the study database and coded using the medical dictionary for regulatory activities (MedDRA) prior to database lock.

Participant evaluation of intervention acceptability and tolerability will be captured on paper questionnaires, and these data will then be entered at site onto RCC. The views of healthcare professionals involved in the study will be captured anonymously via a survey completed and held within RCC. Focus groups will be audio or video recorded and transcribed verbatim, and resulting transcripts labelled with unique identifiers ready for analysis. Audio/video recordings and the resulting anonymised transcripts will be held in the secure HHTU instance of Box.com collaborative cloud file storage system. Original audio/video recordings will be destroyed once transcription is completed and allocation of unique identifiers has been assigned.

Glucocorticoid results from analysis of serum and saliva samples received from the central lab will be uploaded in a lab report to a dedicated (user access-restricted) secure location on Box. The HHTU data team will perform an initial check prior to data entry into RCC and an independent second check in RCC once data has been added.

eConsent signatures and associated data will be captured using DocuSign cloud-based signature platform. Although copies of consent forms will be stored on Box, they will not be exported as part of the final trial dataset.

The database will be locked to obtain the final dataset after trial completion and resolution of all data queries. A copy of the final trial dataset and notification of completion of trial visits will be sent to the Sponsor before the randomisation list can be released to HHTU prior to statistical analysis. Locked study datasets will be exported from RCC and transferred via a secure folder in Box to the trial statistician at the University of Sheffield and the qualitative researcher at Sheffield Teaching Hospitals NHS Foundation Trust for analysis in compliance with GDPR 2018. A copy of each individual site’s data will be sent to the site, and a copy of the final trial dataset will be archived by HHTU.

### Statistical analysis

Statistical analysis will follow the methodology detailed in the study-specific statistical analysis plan.

#### Blind data review

While no formal interim analysis is planned, the trial statistician will perform a quality control check on cortisol and cortisone values derived from each batch of study samples throughout the data collection phase and prior to provision of the final dataset. Individual visit data will be treated as completely independent (no within-participant linkage across visits) with original participant ID numbers removed from the dataset to preserve blinding. Spaghetti plots of all timepoints within each visit will be created and grouped by endpoint—serum cortisol, salivary cortisol, salivary cortisone. Any anomalies noted will be explored and resolved prior to database lock.

#### Final analysis

The full analysis set (FAS) will include all participants who have had at least one dose of study treatment (Nasacthin or Synacthen) and have at least one observation of serum cortisol or salivary cortisone. This is a modified intention-to-treat analysis set as participants who do not receive any treatment or who do not provide any cortisol/cortisone observations will not be included in the analysis. This analysis set will be used for the analysis of all efficacy data.

The Per-protocol Analysis set will include all participants who are deemed to have no important protocol deviations that could interfere with the primary objectives of the study. This is a sub-population of the FAS.

The safety analysis set (SAS) will include all participants who have received at least one dose and will be used for the analysis of safety data (AEs).

Continuous data will be summarised using n, mean, SD, median, minimum and maximum. Lower and upper quartiles may also be calculated as necessary. Demographics and any baseline characteristics will be summarised overall for the SAS. Medical history, which will not be coded, will be listed but not summarised.

All available data will be included in each analysis. The key timepoint for analysis is the 30 min post-administration of either IMP. A participant does not need to have provided data at every time point after every treatment to be included in the analysis, therefore it is possible that the number of participants included in each analysis may vary.

All study participants will be re-assessed for AI as part of the trial using the SST. A diagnostic serum cortisol cut-off of ≤429 nmol/L will be the reference standard result, which will be used for the calculation of the PPA. The proportion will be calculated together with a 95% exact CI using the Clopper-Pearson method.

Analysis for the primary objective will include the subset of the FAS who fail the SST (ie, have AI) and have provided a serum cortisol sample at 30 min post-Nasacthin dose; any participants in the FAS who pass the SST or who have not provided a post-Nasacthin serum cortisol sample will be summarised.

The PPA calculation for the primary outcome analysis will then be repeated using serum cortisol levels obtained on the Nasacthin test at 60 min compared with the SST result at both 30 and 60 min.

The safety of Nasacthin will be assessed by reporting on the frequency of AEs, SAEs and SUSARs by treatment. AEs, SAEs and SUSARs will be summarised by treatment received, system organ class and preferred term. If there are very few AEs (eg, ≤8), then they will be listed only. Graphical summaries will be considered if the number of AEs is large.

For the exploratory objective, the serum cortisol, salivary cortisol and salivary cortisone responses at 30 and 60 min after each of the active treatments will be summarised using n, mean, SD, median, minimum and maximum.

#### Sensitivity analysis

If participants report coryzal symptoms starting within 24 hours of the visit, these will be recorded and summarised. A sensitivity analysis may be carried out for the primary objective excluding observations taken at these visits if there is a concern that inflamed mucus membranes may impact how the nasal drug works.

### Qualitative research analysis

Analysis of participant and healthcare professional perspectives on acceptability, tolerability and usability of the Nasacthin test will be reported using descriptive statistics by calculating rates and percentages. Open-ended text boxes will be analysed using content analysis and coded into a range of categories using NVivo. Thematic analysis on transcripts from participant and stakeholder focus groups will be completed using NVivo.

### Patient and public involvement and engagement (PPIE)

Through consultation with the Lay ADvice on Diabetes and Endocrine Research (LADDER) patient and public involvement and engagement (PPIE) group at Sheffield Teaching Hospitals NHS Foundation Trust and PPIE groups at Sheffield Children’s Hospital, cohorts of adult and paediatric patients with experience of the SST and/or salivary tests were convened to explore the unmet needs in greater depth and develop the research design.

Subsequent meetings with the LADDER group and additional Sheffield Children’s Hospital PPIE groups have been used to facilitate the co-production of trial documentation. The study team will provide updates on trial progress and further input will be sought from these groups to discuss any delivery issues, topic guide development for the participant and stakeholder focus groups and assist in plans for dissemination of results.

Additionally, two PPIE representatives serve as key members of the independent Trial Steering Committee to provide valuable patient perspective.

## Ethics and dissemination

### Regulatory approvals

The trial protocol and subsequent amendments have been reviewed and approved by the South Central-Hampshire A Research Ethics Committee (REC ref. 24/SC/0102) and by the Medicines and Healthcare Products regulatory Agency (MHRA) and HRA. The ISRCTN registry will be updated in accordance with any amendments to the study.

### Trial oversight

Sheffield Children’s NHS Foundation Trust is the study sponsor, and HHTU is responsible for trial implementation and management and will perform central and site monitoring in accordance with a sponsor-approved trial monitoring plan.

A trial management group (TMG) has been convened and meets regularly to oversee trial delivery and operations. An independent Trial Steering Committee (TSC), comprising two expert clinicians, a statistician, a trials methodologist and two PPIE representatives, will provide overall trial supervision and advice on behalf of the sponsor and project funder and hold executive power on key trial-related decisions. An independent data monitoring and ethics committee (DMEC), comprising two expert clinicians and a statistician, will monitor progress, review efficacy and safety data, and make recommendations to the TSC on study conduct and continuation where necessary.

### Safety considerations

Participants will be monitored for any AEs throughout their study visit and checks will be made during follow-up telephone calls. Any symptoms known to be associated with nasal drug administration will not be reported as AEs unless persistent (defined as still present 30 min after IMP administration).

SAEs are not anticipated during the trial due to the well-established safety profiles of the main IMP ingredients, that is, tetracosactide and chitosan. There will be a robust SAE reporting process in place, with reporting via the study database and automatic alerts to the study team.

The AE reporting period begins from the point of consent and ends 48 hours after the final trial visit. Participants will be advised to contact the study team if they experience any AEs within this period.

The occurrence of one possibly related serious AE or two possibly related severe AEs will trigger trial stopping criteria. The trial can only be restarted following discussion with the DMEC and MHRA approval of a substantial amendment.

If a possibly related serious or severe AE occurs in any individual participant, they should not receive any subsequent IMP and will be withdrawn from the trial.

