Rapid enzymatic conversion of cortisol in saliva to cortisone due to expression of 11β-hydroxysteroid dehydrogenase type 2 in salivary glands means that the concentration of cortisone is typically 4 to 6 times higher than that of cortisol in saliva^10 19^ and is detectable at low serum cortisol levels.^13 14^ Salivary cortisone has been found to exhibit a better and more linear correlation with serum total cortisol than salivary cortisol^13 14 20^ and, as such, salivary cortisone is generally considered the preferred salivary biomarker for AI diagnosis.^9^ A recent NICE evidence review recommended further research on the clinical and cost-effectiveness of salivary cortisone/cortisol for AI diagnosis.^21^

The Nasacthin test has been developed as a non-invasive alternative to the SST stimulation test. The tests both use the same active pharmaceutical ingredient, tetracosactide, but in Nasacthin this is combined with a mucoadhesive agent, chitosan, to aid nasal absorption, and is delivered intranasally via a spray. Resultant glucocorticoid levels (cortisol and cortisone) can be measured in serum, but to render the test needle-free, saliva samples can be collected to quantify the adrenal response.

Nasacthin has been trialled over four open-label multi-arm sequence-randomised crossover pharmacodynamics studies^22^ across which a total of 70 doses of Nasacthin were administered to healthy males and children of both sexes. In these studies, it was found to be reliably absorbed, demonstrating a comparable plasma cortisol response to the IV SST at 60 min (the optimal timing of salivary glucocorticoid sampling following stimulation with IV Synacthen^17^), and well-tolerated with no serious adverse event (SAE) reports. Any AEs recorded were anticipated following nasal drug administration and were mild with full and rapid resolution.

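### Leaving nasal symptoms gone by 30 minutes out of AE reporting means the by-treatment AE frequencies can only understate Nasacthin's transient local events

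*Protocol article*

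**What the plan says.** All references are to the Protocol article.

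- **Safety considerations** sets the exemption: "Any symptoms known to be associated with nasal drug administration will not be reported as AEs unless persistent". Persistent is "defined as still present 30 min after IMP administration".
- **Trial outcomes and assessments** describes collection without any exemption: "Details of all harms or unintended effects occurring during trial participation will be collected and used to determine the frequency of AEs", broken down by treatment arm.
- **Final analysis** names the safety measure: "The safety of Nasacthin will be assessed by reporting on the frequency of AEs, SAEs and SUSARs by treatment". It adds: "If there are very few AEs (eg, ≤8), then they will be listed only".
- **Trial investigational medicinal product (IMP)** says that Nasacthin "will be administered via a primed intranasal Mucosal Atomisation Device". Synacthen is an intravenous bolus through the cannula.
- **Background and rationale**, on the earlier studies with 70 Nasacthin doses: "Any AEs recorded were anticipated following nasal drug administration and were mild with full and rapid resolution".
- **Safety considerations** also builds a stopping trigger on AEs: "The occurrence of one possibly related serious AE or two possibly related severe AEs will trigger trial stopping criteria". A related sentence withdraws an individual after a possibly related serious or severe AE.

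**The concern.** The AE table is where a reader will look for the harms of the nasal product relative to the intravenous one. The exemption is tied to nasal administration, so in practice it takes events from one column of that table and not from the other. A nasal symptom that settles after 20 minutes at a Nasacthin visit is not reported as an AE. On the text of the article, a cannula-site or injection symptom of the same duration at a Synacthen visit is.

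The removed class is also the class that earlier experience points to: the earlier nasal-type events were recorded as AEs, and were mild and short-lived.

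The trial is meant to support a regulatory application, and the article lists detailed safety and tolerability data among its strengths. An AE table that leaves out transient local symptoms without saying so would give an incomplete picture of what the product does to the person receiving it. If the symptoms are never recorded in a structured way, no later analysis can restore them.

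**Working it through.** The plan states no figure for this point, so there is none to reproduce. The check has two parts.

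**1. The sections set side by side**

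- *Scope.* Take a known nasal symptom that resolves at 20 minutes. Under Trial outcomes and assessments it is an unintended effect and enters the AE frequency. Under Safety considerations it is not reported as an AE. Both cannot govern the same table.
- *Direction.* The exemption removes events and never adds any, so the recorded Nasacthin frequency is at or below the one with all symptoms counted. This needs no assumed rates. For the Nasacthin-minus-Synacthen difference it needs only that the exempt symptoms are at least as common after the nasal product as after the intravenous one.
- *Severity.* The exemption, as stated, has a time limit but no severity limit. A severe, non-serious nasal symptom that resolves within 30 minutes would not be reported as an AE. It is therefore unclear whether it counts towards the severe-AE stopping and withdrawal wording in the same section.

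**2. Illustration of size (rates are assumptions)**

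Inputs: N = 32 completers (Sample size section); b = risk of any other AE at a visit, same for both products; q = risk of a nasal symptom after Nasacthin, taken as zero after Synacthen; s = share of those symptoms gone by 30 minutes. Nasal symptoms and other AEs are taken as independent.

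- AE risk on Nasacthin, all symptoms counted: 1 − (1 − b)(1 − q)
- AE risk on Nasacthin, under the rule: 1 − (1 − b)(1 − q(1 − s))
- AE risk on Synacthen: b
- Nasacthin participants left out of the AE count: N(1 − b)qs

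With b = 5%, q = 30%, s = 80%:

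- All counted: 1 − 0.95 × 0.70 = 0.335, a difference from Synacthen of 28.5 points.
- Under the rule: 1 − 0.95 × 0.94 = 0.107, a difference of 5.7 points.
- Left out: 32 × 0.95 × 0.30 × 0.80 = 7.3 participants.

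| q | s | Difference, all counted | Difference, under the rule | Left out of 32 |
|---|---|---|---|---|
| 10% | 50% | 9.5 points | 4.8 points | 1.5 |
| 30% | 80% | 28.5 points | 5.7 points | 7.3 |
| 30% | 100% | 28.5 points | 0 | 9.1 |
| 50% | 100% | 47.5 points | 0 | 15.2 |

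Raising b to 10% changes little: at q = 30% and s = 80% the differences are 27.0 and 5.4 points, with 6.9 participants left out.

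For the listing threshold, at b = 5%, q = 30%, s = 80%, the expected number of participant-visits with an AE falls from 32 × (0.335 + 0.05) = 12.3 to 32 × (0.107 + 0.05) = 5.0. The threshold counts AEs rather than participant-visits, so this shows only that the rule makes a listing without a summary more likely.

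**The case against.** The other side has substantial points, and several of them limit the concern.

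- *A reader might infer that the Nasacthin AE table will be nearly empty by definition.* The documents do not support that. Nasal symptoms still present at 30 minutes, events reported at the 24–48 hour call and all non-nasal events remain AEs. The background section speaks of rapid resolution but gives no minutes, so it is not shown that the earlier events would have fallen under the rule.
- *A reader might infer that brief symptoms go entirely uncaptured.* The rule says they are not reported as AEs; it does not say they are not noted anywhere. Participants complete a tolerability questionnaire at the end of each visit and a comparison of the two tests at the final visit. These may pick up some transient discomfort. They are non-validated and are analysed apart from the AE tables, so they soften the gap but do not close it.
- *A reader might infer that hypersensitivity reactions are exempt because close monitoring covers the same 30 minutes.* Nothing classes such a reaction as a known nasal-administration symptom. Harms considered serious must be logged within 24 hours, in wording not confined to reported AEs. The open question for the stopping text is therefore narrow: severe, non-serious, purely nasal and brief.
- *The article condenses a fuller protocol.* A matching rule for cannula symptoms, or a severity limit, may stand there. This is fair, and the point is confined to what the article states. The exemption itself and its conflict with the outcomes section are stated text, not omissions.
- *The rule is openly prespecified, the comparison is descriptive and the protocol was approved.* All true. Openness in the protocol does not make the table symmetric, and approval does not reconcile two sections that disagree.
- *The listing threshold is given only as an example, and a listing shows each reported AE.* Agreed; this is a minor consequence. A listing cannot show the exempt symptoms either.

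**Conclusion.** The concern holds in a limited form. As stated in the article, the exemption can only lower Nasacthin's recorded frequency of transient local events. It has no stated counterpart for the intravenous product, and it conflicts with the sentence under which all harms feed the AE frequency.

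The direction follows from the text. The size does not: the documents give neither the rate of nasal symptoms nor the share that resolves by 30 minutes. The range of about 1.5 to 15 of 32 participants rests wholly on the assumed rates and on independence, and should not be read as an estimate.

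The effect is on descriptive safety frequencies. No formal test and no part of the primary agreement analysis is affected. The unclear link to the severe-AE stopping and withdrawal wording is an ambiguity to be reconciled, not a demonstrated failure of safety oversight.

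**What to change.** 1. Record nasal and administration-site symptoms at both visits, whatever their duration, with severity, onset and resolution time.
2. Tabulate the transient ones by treatment beside the AE table. Keep 30 minutes as a flag for persistence, so the planned distinction is not lost.
3. State in the AE table what it excludes.
4. Reconcile the exemption in Safety considerations with the collection statement in Trial outcomes and assessments, and with the severe-AE stopping and withdrawal wording. What that clinical wording should be is for the sponsor and its committees; none is proposed here.

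The cost is a short form page, one extra table and a wording change to the protocol. The Nasacthin symptom profile will look less favourable. Recruitment opened on 5 February 2025, so visits already completed may lack this detail; the extra table should say from which visits the symptoms were recorded systematically.
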